### Usual care group (control)

Participants randomly assigned to the usual care group will follow the general advice from the physiotherapists about the positive effects of PA. They will perform 40–45 min/day, 5 days a week, of small active and passive movements applied as a series of gentle stretches in a smooth, rhythmic fashion to the individual joints. They will also perform aerobic activities such as walking for 5–10 minutes at low intensity-intensity exercise. Intensity [expressed as rate of perceived exertion (RPE)] will range from 9 to 11 in the Borg's conventional (6–20 point) scale [41]. These RPE values correspond to a subjective perceived exertion of "very light – gentle walking" and "fairly light" respectively.

### Intervention (training)

Participants allocated in the intervention group will be enrolled in three weekly non-consecutive training sessions for 8 weeks. Each session will last for about 45–50 min. The exercise program will consist of muscular strength and aerobic exercises. Each session will start and end with a low intensity ~5–7 min warm-up and cool-down period respectively, consisting mainly of stretching exercises involving all major muscle groups.

The core portion of the training session will consist of strength training engaging the major lower limb muscles, i.e. leg press exercise performed with variable resistance weight machines (Technogym, Barcelona, Spain). The participants will perform one set of 8–10 repetitions with resting periods of 1–2 min between exercises. The load will be gradually increased as the strength of each person improves, i.e. from 30% of 1 repetition maximum (1RM) at the start of the program to 70% of 1RM at the end. Resistance training will also include one set of 8–10 repetitions of biceps curls, arm extensions, arm side lifts, shoulder elevations, seated bench press and seated lateral row. For these exercises, we will use barbells (1–3 kg per exercise) or low-to-medium resistance bands (Therabands). We will also include handgrip exercises with foam balls (3 repetitions of 10 seconds each). Stretching exercises of the muscles involved in the previous exercises will be performed during the rest periods. Participants will be given advice to complete all movements in a slow, controlled fashion, and to not to hold their breath during the exercises.

Aerobic training will be executed in a cycle ergometer (Bike Excite Forma, Technogym, Barcelona, Spain) and will include ~5 minutes (at the start of the program) to ~15 minutes of moderate-intensity exercise. Intensity (expressed as RPE) will range from 12 to 13 in the Borg's conventional (6–20 point) scale [41]. These RPE values correspond to a subjective perceived exertion of "light" and "somewhat hard" respectively. Overexertion will be checked by the "Talk test" [42]. All sessions will be performed in the exercise training facilities from the geriatric nursing home *Los Nogales-Pacífico *(Madrid, Spain).

Participants in the training group will also join to the activities performed by the usual care group two days per week.

### Participant retention and adherence

To reduce participants drop out and to maintain adherence to the training program, all sessions will be accompanied with music [43], and will be performed on an airy, well lighted exercise room. Qualified fitness specialists will carefully supervise every training session and will work with groups of 2–3 persons to ensure that participants are performing the exercises correctly.

### Primary outcome measures

#### Quality of life (QOL) and well-being

We will assess participants' QOL with the Spanish version of the Short Form-12 items (SF-12), which has shown its validity in the Spanish population [44]. We will also assess a life satisfaction index with the EuroQol instrument [45], and depressive symptoms by the geriatric depression scale [46].

#### Daily physical functioning

We will assess participants' balance and walk abilities using the *Tinetti scale *[37]. This is a simple, easily administered test that measures a patients' gait and balance. It uses a three-point ordinal scale, ranging from 0–2 where "0" indicates the highest level of impairment and "2" the individual's independence. Interpretation of scores is provided as low, medium, or high fall-risk. For balance evaluation, the subject is seated in a hard, armless chair and the following manoeuvres are tested: sitting balance, arises, attempts to arise, immediate standing balance (first 5 seconds), standing balance, 'nudged', eyes closed, turning 360 degrees and sitting down. The maximum sum-score of both gait and balance components is 28 points. Patients who score below 24 are at risk for falls, and the risk of falling is high with a score below 19. The validity of this test for screening old adults at risk for falling is well established [47].

The *Barthel index *is a valid instrument that is widely used to measure the capacity of a person for the execution of ten basic activities in daily life, obtaining a quantitative estimation of the subject's level of independency [48,49]. The ten items include: eating, transferring from bed to chair, using the toilet, bathing/showering, personal hygiene (tooth brushing, shaving) dressing, walking, stair climbing, and bowel and bladder control. Each individual item is scored with 0 (unable to perform without complete help or fecal/urine incontinence), 5 (able to perform the activity with little help or only accidental fecal/urine incontinence) or 10 (able to perform without any help or total fecal/urine continency). The sum-score ranges from 0 (*totally dependent*) to 100 (*totally independent*).

#### Muscular strength

Dynamic muscular strength of the lower body will be assessed following a standardized strength testing protocol, i.e. 1RM seated leg press, using the aforementioned variable resistance weight machines. The 1RM leg press test is a valid means to assess leg muscle strength in elderly men and women [50]. Initial loads will be 70–100% of body weight. Following a brief rest period, increments of 2–4 kg will be added until maximal effort is achieved for each lift, usually after 5 trials or less. All participants should be able to lift the initial load at least one time. Participants will be instructed on proper breathing and lifting form for each movement.

Upper body strength will be assessed with the handgrip strength test [51]. This test is a valid means for assessing upper body strength in the elderly [22,51]. Handgrip strength will be measured using a digital dynamometer (T.K.K. 5101 Grip-D; Takey, Tokyo, Japan), and the scores will be recorded in kilograms (0.1 kg). When performing the measurement, participants will be instructed to maintain the standard bipedal position during the entire test with the arm in complete extension and will not be allowed to touch any part of the body with the dynamometer except the hand being measured. Each subject will perform (alternately with both hands) the test twice, and allowing a 30–60 seconds rest between the measurements. For each measure, the hand to be tested first will be chosen randomly. The grip span of the dynamometer will be adjusted to the individual's hand size [51].

#### Ambulation ability

We will use a (i) 8-meter walk test and (ii) 4-step (20-cm height each) stairs test, both of which have proven useful to determine leg extension power and functional mobility in the elderly [52]. All the participants will use hand railing while ascending and descending the stairs to diminish the risk of falling. Performance time in all the tests will be measured by the same investigator with the same stopwatch to the nearest 0.1 s.

### Secondary outcome measures

#### Anthropometry

Standing height will be measured to the nearest 0.1 cm with a clinical stadiometer (Asimed T2, Barcelona, Spain) while the person is standing barefoot. Body mass will be determined to the nearest 0.05 kg using a balance scale (Ano Sayol S.L., Barcelona, Spain) with the person in her/his underwear. Body mass index (BMI) will be calculated as weight/height (kg/m^2^). Skinfold thickness will be measured with a Harpenden caliper at biceps, triceps, subscapular, abdominal, and suprailiac area at the left side of the body according to the criteria described by Lohman et al. [53]. We will estimate lean and fat mass according to Durnin et al. [54]. Waist circumference will be measured level with the umbilicus. These anthropometric measures are valid to assess body composition in the elderly [55]. To ensure a good reliability, all anthropometric measurements will be performed in triplicate by the same experienced researcher.

#### Physical activity (PA)

We will assess PA with a uni-axial accelerometer (Actigraph MTI, model GT1M, Manufacturing Technology Inc., Fort Walton Beach, FL, USA) which is a valid and reliable tool to asses physical activity [56,57]. Technical specifications and performance properties of this instrument have been described elsewhere [56,57]. A 60 seconds epoch will be used in this study. Participants will be instructed to place the monitor at the lower back, using an elastic waist band and wear it for seven consecutive days. They will be also instructed to wear the accelerometer during all time awake and only to remove it during water based activities.

A measure of total volume of activity (so called average intensity of PA) will be expressed as the sum of recorded counts per epoch divided by total daily registered time. We will also obtain the following measures: time spent inactive, total time in light, moderate, and vigorous intensity PA. We will calculate the time spent in at least moderate PA (so called 'moderare-to-vigorous PA' or 'MVPA'). Inactivity will be classified as activity below an arbitrary level of 100 counts per minute, including sporadic zero values less than 20 continuous minutes [58]. The cutoff points for light, moderate and vigorous PA will be set to 100-1951, 1952-5724 and ≥ 5725 counts per minute respectively [56]. A measure of total activity will be expressed as average intensity from the activity monitor and determined as the total counts per day divided by registered time (counts per minute).

We will also assess Cognitive impairment through the Mini-Mental State Examination (MMSE) [59].

### Familiarization and reliability assessment

Before the start of the study all subjects will have a familiarization period with all the tests, consisting of three ~30-min sessions. Each session will be preceded by a warm-up and will end with a cool-down of the same activities and duration used during the training period. Each familiarization session will consist of 2–3 sets of 1–3 repetitions of the exercises. We will also assess test-retest reliability for each outcome measure.

### Assessment of side effects

We will also ascertain adverse events, including muscle pain, fatigue, and general aches and pains by self-report during the study period. We will also record the falls over the study period and 1 week after. The mean incidence of falls in nursing homes is 1.5 falls per bed per year (range 0.2–3.6). Fall rates in residential care is 1.5 falls per bed per year (range0.2–3.6) and it certainly depends on the state of fragility of the person [60]. The most successful strategies for fall prevention include interventions to improve strength and functional status, reduce environmental hazards, and monitoring of high-risk residents [60]. In our study, we will define falls as "unexpected event in which the participants come to rest on the ground, floor, or other lower level" [61,62]. An independent researcher will be in charge of auditing all nursing and medical records to record all falls in the participants over the study period.

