### Study participants and selection criteria

STRONG participants include 60 community-dwelling elderly people aged 90 years or over recruited from a geriatric nursing home (Los Nogales-Pacífico, Madrid, Spain). All participants received a comprehensive medical examination.

The inclusion criteria for STRONG are:

- Age: 90 years or over.

- Planning to stay in the same nursing home during the study.

- Able to ambulate, with or without assistance.

- Able to communicate.

- Informed consent: Must be capable and willing to provide consent.

The exclusion criteria for STRONG are:

- Acute or terminal illness.

- Myocardial infarction in the past 3 months.

- Not capable to ambulate.

- Unstable cardiovascular disease or other medical condition.

- Upper or lower extremity fracture in the past 3 months.

- Severe dementia.

- Unwillingness to either complete the study requirements or to be randomised into control or training group.

- Presence of neuromuscular disease or drugs affecting neuromuscular function.

Figure 1 illustrates the participant flow from recruitment to randomisation.

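### The independent record audit covers falls only, so medical adverse events rest on participants' self-report and may be missed, possibly to a different degree in each arm

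*Protocol article*

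**What the plan says.** Under Assessment of side effects, the Protocol article sets out two routes for harms.

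- **Adverse events in general:** "We will also ascertain adverse events, including muscle pain, fatigue, and general aches and pains by self-report during the study period". No other source is named for events that are not falls.
- **Falls:** "We will also record the falls over the study period and 1 week after". For these there is also a record source: "An independent researcher will be in charge of auditing all nursing and medical records to record all falls in the participants over the study period".

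On who is enrolled, Study participants and selection criteria excludes "Severe dementia" without giving a cut-off on a cognitive scale. It also requires participants to be "Able to communicate" and to have the capacity to consent. The Mini-Mental State Examination is recorded (end of the Physical activity section), but the score is not linked to how harms are collected.

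On contact with staff, Participant retention and adherence says of the training arm: "Qualified fitness specialists will carefully supervise every training session and will work with groups of 2–3 persons". Randomisation and blinding accepts that training staff will know the allocation. Usual care group (control) describes activity on 5 days a week and does not say how it is supervised.

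**The concern.** Self-report suits pain and tiredness. It is a weak source for medical events: a participant may forget an infection, may be in hospital when asked, and cannot report their own death. Among nursing-home residents over 90, some of whom may have mild or moderate impairment, that weakness is more than theoretical. Yet a researcher outside the treatment team will already have the records open and is asked to take only falls from them.

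The second issue is comparability. If trainers hear of complaints and absences in one arm through a route that the other arm lacks, a between-arm comparison of harms mixes the effect of exercise with the effect of closer observation. Incomplete capture could hide a real harm. Unequal capture could make training look more harmful than it is. The programme raises leg-press loads to 70% of one-repetition maximum in very old people, so readers will look closely at its safety account.

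**Working it through.** The plan states no figure on this point, so the check sets the sections side by side.

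**1. Source by type of event (Assessment of side effects)**

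| Event | Self-report | Record audit |
|---|---|---|
| Muscle pain, fatigue, aches | yes | no |
| Falls | not specified | yes |
| Illness, injury, cardiovascular event, hospital transfer, death | only source named | no |

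The last row is the gap. The records are read in full, so the limit lies in what is extracted and not in access.

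**2. Who may report poorly.** Three criteria bear on cognition: severe dementia excluded, ability to communicate required, capacity to consent required. Together they bound the degree of impairment but leave mild and moderate impairment eligible. The Discussion lists forgetting among the main reasons for missed training sessions.

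**3. Contact by arm**

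- Training: 3 supervised sessions a week plus 2 days a week in the usual-care activities, so 3 + 2 = 5 days.
- Control: 5 days a week.

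The number of scheduled days is about equal. What differs on the page is the kind of contact: groups of 2–3 with unblinded specialists, and follow-up of absences. The Discussion shows that this route works. It reports respiratory infections and night-time falls because they explained missed training sessions, and an eye operation because it ended one person's training. It reports no such events for controls.

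**4. Window.** Falls are to be recorded for the study period and 1 week more, but the audit sentence names the study period only. The extra week therefore has no stated record source.

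**5. How the result depends on unknowns.** The documents give neither the share impaired, nor the completeness of self-report, nor true event rates. Every input below is an assumption except n = 30 per arm.

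- Overall capture = m × s + (1 − m) × 0.9, where m is the share impaired, s the fraction of events they report, and 0.9 the fraction the others report.
  - m = 0.2, s = 0.8: 0.16 + 0.72 = 0.88.
  - m = 0.6, s = 0.4: 0.24 + 0.36 = 0.60.
- Apparent risk ratio with equal true risk = capture in training ÷ capture in control. With a true risk of 30%, each arm of 30 has 9 events. Training capture is held at 90%, so 8.1 are seen.
  - Control capture 90%: 8.1 seen, ratio 0.9 / 0.9 = 1.00.
  - Control capture 70%: 6.3 seen, ratio 0.9 / 0.7 = 1.29.
  - Control capture 50%: 4.5 seen, ratio 0.9 / 0.5 = 1.80.

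The lines show only that the answer runs from no distortion to a large one, depending on inputs that nobody has.

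**The case against.** The case on the other side has several parts.

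- **The named events are symptoms.** Muscle pain, fatigue and aches are best taken from the participant, and mild soreness may never reach a nursing chart. This stands. A reader might infer that records should become the main source for all adverse events, but that could lose the very complaints most plausibly caused by training.
- **Controls are not out of sight.** A reader might infer that controls have no comparable contact. The schedule contradicts that, with 5 days of activity a week in both arms. The same self-report method is stated for everyone, and randomisation should balance cognition. This stands, but randomisation does not balance how closely people are observed.
- **Severe dementia is not the only cognitive limit.** The communication and consent criteria also restrict who enters. This stands, and it narrows the concern without removing it.
- **A journal article leaves adverse-event forms and serious-event procedures to a fuller protocol.** This is fair for forms and timing. But the article does state a source for adverse events and does state the purpose of the audit, so the point concerns what is written and not what is absent.
- **Investigators evidently do hear of medical events.** They do, but the examples in the Discussion all come from the training arm, so they do not show equal capture.
- **Safety is not a listed outcome, and no between-arm safety test is planned.** Correct. The efficacy conclusions are unaffected.
- **The audit window may be loose wording.** It may, and one clause settles it.

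**Conclusion.** The point holds as a cheap improvement to a stated design choice. Medical events other than falls have self-report as their only named source, in a population where some participants may be poor reporters, while records that would show such events are already being read for falls. Capture may also differ by arm through the closeness of supervision and the tracking of absences, most plausibly towards more events recorded in the training arm.

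A reader might go further and conclude that harms are under-counted, or that they are collected unequally, or might put a percentage on the loss. The documents support none of these. They give no prevalence of impairment, no reporting rate and no event counts by arm, and they do not describe how control sessions are supervised. The size cannot be computed, and the illustrative figures in the working carry no weight as estimates. The conclusion assumes only that the nursing and medical records note medical events at least as reliably as residents recall them, and that the article's description of the audit is complete on its purpose.

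**What to change.** Amend Assessment of side effects in four ways.

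1. Have the same independent researcher extract illness, injury, cardiovascular events, hospital transfers and deaths, as well as falls, from the records already being read.
2. Apply identical extraction rules in both arms, without knowledge of allocation where the record permits. The section does not say whether this researcher is blinded.
3. Run the audit through the week after the study period, so that it matches the window for falls.
4. Keep self-report as the source for muscle pain, fatigue and aches, with the same questions put at the same times in both arms.

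The cost is additional extraction time for a researcher who is already assigned, and a fixed question schedule for symptoms. The audit needs no new staff, visits or procedures.

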## Discussion

Up to April 2009, 58 nonagenarians living in the aforementioned geriatric nursing home meet all the eligibility criteria. Forty-eight of them originally gave their written permission to participate in the study in the previous months. Of these 48 persons, six who were allocated to the control group finally refrained from participating in the study. One participant assigned to the training group had to drop-out from the program after having completed only one training session due to eye surgery. The number of participants who are currently participating in the study within the control and intervention group is n = 12 (2 men and 10 women, mean (SD) age: 92 (3) years, range 90 to 97 years) and n = 18 (3 men and 15 women; mean age: 92 (2) years, range 90 to 96 years) respectively. All these 30 participants successfully completed all of baseline evaluations, included all the strength and functional tests. Of the total of 24 training sessions that we programmed for each participant in the training group, the 19 subjects who are currently in this group have performed an average of 10 sessions, with a mean adherence of 87%. Main reasons for missing a training session were mild upper respiratory tract infections, falls (at night, out of training sessions) or simply forgetting. We noted no major health problem (included absence of falls) associated with the baseline strength tests or training sessions, expect mild muscle pain in some participants.

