**Methods:**

Sixty (51 women) nonagenarians (age range: 90–102 years) who live in a geriatric nursing home will be randomly assigned to either a usual care (control) group (n = 30) or an intervention (training) group (n = 30). Participants allocated in the usual care group will receive general physical activity guidelines and participants allocated in the intervention group will also enrol in three weekly non-consecutive individualized training sessions (~45–50 min each) during 8 weeks. The exercise program will consist of muscular strength [with a special focus on leg press at 30% (start of the program) to 70% 1 repetition maximum (end)] and aerobic exercises (cycle-ergometry during 3–5 to 15 minutes at 12–14 points in the rate of perceived exertion scale).

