### Sample size and statistical power

The required sample size was determined for one of the primary outcome variables, i.e. functional capacity using the Tinetti scale [37]. We believe that a clinically relevant change is a ≥ 30% increase in the aforementioned scale. We expect the control group to improve ~0 to 5%; thus, we can detect differences of at least ≥ 35% with a power > 80% and an α of 0.05 with two groups of 25 subjects. Assuming a maximum loss of follow-up of 20%, we will recruit a total of 60 nonagenarians. We will be also able to detect a significant difference of 4 points in the Tinetti scale with this number of participants, assuming a standard deviation of 5 points.

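### The planned 60 participants and the power stated for them are not reconciled with the article's own April 2009 status: 58 eligible, 48 consenting, 30 active (12 control, 18 training)

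*Protocol article*

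**What the plan says.** The abstract gives the sample as "Sixty (51 women) nonagenarians (age range: 90–102 years) who live in a geriatric nursing home will be randomly assigned", 30 to each arm. The section on study participants and selection criteria likewise describes 60 people, from one named nursing home. The sample size section says "we can detect differences of at least ≥ 35% with a power > 80" per cent, with "two groups of 25 subjects". After an allowance of up to 20% for loss to follow-up, it says "we will recruit a total of 60 nonagenarians". It adds that the trial will be "able to detect a significant difference of 4 points in the Tinetti scale" with this number, taking an SD of 5 points.

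The Discussion reports on the same home up to April 2009: "58 nonagenarians living in the aforementioned geriatric nursing home meet all the eligibility criteria". Of these, 48 gave consent. Six allocated to control then declined to take part, and one training participant dropped out. It continues: "The number of participants who are currently participating in the study within the control and intervention group is n = 12" for control and 18 for training. Two sentences later the training group is given as 19.

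The study design section runs the study from March to September 2009, with 8 weeks of follow-up. The article mentions no second recruitment wave, no other site, and no revised target or power.

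**The concern.** The article prints two sets of numbers for one source population and does not connect them. The target of 60 is larger than the pool found eligible by April. The 48 who consented are fewer than the 50 evaluable participants that the calculation needs, even if none is lost. The arms now active are well below 25 and unequal.

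The Tinetti scale is a primary outcome and the one that sets the sample size. If the power above 80% and the 4-point detectable difference stand unchanged while the trial finishes near the reported numbers, a non-significant Tinetti result could be read as firmer evidence against a benefit than the data can give.

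**Working it through.** **Inputs.** Difference 4 points, SD 5, alpha 0.05 and 25 evaluable per arm come from the sample size section; the counts come from the Discussion. Sidedness is not stated, so two-sided is assumed. SD 5 is taken as the SD in a two-sample t-test.

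**Reproducing the plan.** n per arm = 2 × SD² × (1.960 + 0.842)² / difference² = 2 × 25 × 7.85 / 16 = 24.5, rounded up to 25. Power at 25/25 is 80.7% by normal approximation and 79.1% by noncentral t. The plan's figure is reproduced. The 60 is 50 × 1.2.

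The 35% version cannot be checked because no SD is given on the percentage scale. At 25 per arm it needs an SD of about 43 percentage points or less.

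**Applying the same model to the reported counts.** SE = 5 × √(1/n₁ + 1/n₂). The noncentrality is 4/SE, with n₁ + n₂ − 2 degrees of freedom. The last column is the difference detectable with 80% power. At 12/18, for example, SE = 5 × √(1/12 + 1/18) = 1.863, noncentrality = 4/1.863 = 2.15 and df = 28, giving power 54.5%.

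| Scenario | Arms | Power for 4 points | Detectable difference |
|---|---|---|---|
| Planned, no loss | 30/30 | 86% | 3.7 |
| Planned evaluable | 25/25 | 79% | 4.0 |
| All 58 eligible, no loss | 29/29 | 85% | 3.7 |
| All 58 eligible, 20% loss | about 23/23 | 76% | 4.2 |
| 48 consenters, no loss, equal split assumed | 24/24 | 77% | 4.1 |
| 48 less the seven reported losses, equal allocation assumed | 18/23 | 70% | 4.5 |
| 48 consenters, 20% loss | about 19/19 | 67% | 4.7 |
| Currently active | 12/18 | 54% | 5.4 |

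Normal-approximation values are one to three percentage points higher (57% at 12/18).

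**Dependence on the SD.** If SD 5 describes scores and the analysis is of change, the SD of change is 5 × √(2(1 − r)), where r is the pre-post correlation. The documents give no r. Assumed values of 0.5, 0.6, 0.7 and 0.8 give 54%, 64%, 76% and 91% at 12/18. Below 0.5, power falls under 54%. If SD 5 already describes change, 54% stands.

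**The counts in the Discussion.** 48 − 6 − 1 = 41, but 12 + 18 = 30 are active, so 11 consenters are unexplained. The training arm is both 18 and 19; using 19 moves power only to about 55%. Six refusals among the 12 + 6 = 18 controls accounted for is 33%, above the 20% maximum; if 24 were allocated to control it is 25%.

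**The case against.** The strongest reply is that the status report is interim. It runs to April 2009 in a study lasting until September, so there was time for later starters. Eligibility can also change: residents turn 90, and the 3-month infarction and fracture windows expire. This stands. A reader might infer that 60 was unattainable, or that 54% is the power the trial ended with; the documents support neither.

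Nor is 12/18 shown to be the analysed sample. Eleven consenters may be waiting, unallocated or lost. The statistical analysis section specifies intention-to-treat with multiple imputation, so the seven known losses would stay in the analysis set. Imputation does not, however, restore the information lost with unobserved outcomes.

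The planned analysis is a group-by-time repeated-measures ANOVA, and the article does not say whether SD 5 is for scores or change. This also stands, and it is why the result belongs in a range.

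Two further inferences should be resisted. The sample size calculation itself contains no error that this point depends on, since 25 per arm is reproduced. And the sex and age figures are weak evidence of conflict: 25 of 30 women (83%) against 51 of 60 (85%), with ages 90–97 lying inside 90–102, could describe a subset of the planned sample.

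Finally, Figure 1 is not visible here and may show part of the participant flow. So the point is not that flow numbers are missing, but that the text carries a target and a status that do not fit together.

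**Conclusion.** The point holds as a failure to reconcile. By April 2009 the home had yielded 58 eligible and 48 consenting residents against a target of 60 and a need for 50 evaluable, and the article leaves target, power and detectable difference unchanged.

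The eligible and consenting counts alone imply a mild shortfall: full retention of 48 gives about 77%, close to the 79% at 25/25. The shortfall becomes material with the plan's own 20% loss (about 67%, detectable difference about 4.7 points) and large if the trial ends with the arms now active (about 54%, about 5.4 points).

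These figures rest on 4 points, SD 5 as a two-sample t-test SD, and a two-sided 0.05 test. The 12/18 result is a low scenario. It rises if more participants join or if SD 5 is a score SD with a high pre-post correlation.

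**What to change.** - Reconcile the planned 60 with the reported recruitment. Account for the 11 unexplained consenters, and settle whether the training arm has 18 or 19.
- Then do one of two things. Either state how and by when the remaining participants will be found, or restate the power for 4 points and the difference detectable with 80% power for the attainable, unequal arms. Give the restatement as a range, and say whether SD 5 refers to scores or change and what correlation, if any, is assumed.
- Bring the sample descriptions in the abstract and in the participants section into line with the result, marking clearly what is target and what is achieved.

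The cost is wording only, with no change to design or conduct unless the sponsor chooses to extend recruitment. If recruitment is not extended, the stated power becomes less favourable.
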